### **Trial design {8}**

This is a randomised controlled trial (RCT) comparing METRA to treatment as usual (TAU), with an embedded qualitative component. Participants will be assessed; 1) at baseline, 2) at post-Module 1, 3) at post-Module 2, and 4) at ~~6-month~~ 3-month follow-up (CHANGE 2: Follow-up was changed to 3-months. This decision was made due to security issues and increased movement within Afghanistan following the change in government). The first three assessments are face-to-face assessment and will include all measures. The follow-up assessments will be conducted by phone/skype/zoom and will include the primary and secondary outcomes. Assessments will be conducted by independent raters who have no therapeutic relationship with participants and are blind to condition.

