**Statistical methods****Statistical methods for primary and secondary outcomes {20a}**

All primary analyses will be on intent-to-treat principle, with all randomized participants analyzed in their allocation condition.

Objective 1 will be examined using linear mixed effects models with intervention type, time, and intervention by time interaction as fixed factors (CHANGE 6: This was changed to generalized estimating equations following reviewer feedback. However, the results were the similar when using linear mixed effects models). Repeated assessments of individuals will be modelled as random intercept. Of primary interest will be the intervention by time interaction, which will compare the levels of change over time in outcomes of the METRA and TAU groups. Levels of significance will be set at  $\alpha < .05$  and hypothesis tests will be 2-sided. Objective 2: Thematic analysis of qualitative data (Atkins et al., 2017; Braun & Clark, 2006; Marks & Yardley, 2004) will assess feasibility and appropriateness.

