**Methods in analysis to handle protocol non-adherence and any statistical methods to handle**

**missing data {20c}**

N/A

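### The primary analysis is written both as GEE and as a random-intercept mixed model, with no missing-data method although attrition is expected

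*Supplement*

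**What the plan says.** All of this is current text in the Version 2 protocol.

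- **Model, {20a}:** "Objective 1 will be examined using linear mixed effects models with intervention type, time, and intervention by time interaction as fixed factors". Superseded words are struck through elsewhere in Version 2 (Objectives 3 and 4, for example), but this sentence is not.
- **In-line note, same sentence (Change 6):** "This was changed to generalized estimating equations following reviewer feedback". It continues: "However, the results were the similar when using linear mixed effects models".
- **Next sentence:** "Repeated assessments of individuals will be modelled as random intercept".
- **Target, {20a}:** "Of primary interest will be the intervention by time interaction".
- **Analysis set, {20a}:** intention to treat, "with all randomized participants analyzed in their allocation condition".
- **Missing data, {20c}:** the item headed "Methods in analysis to handle protocol non-adherence and any statistical methods to handle" missing data is answered N/A.
- **Expected loss:** Sample size {14} adjusts the number for attrition without giving a rate. Trial design {8} explains the shorter follow-up: "This decision was made due to security issues and increased movement within Afghanistan".

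No working correlation, link or variance estimator is given for the GEE, and the mixed model is given no role after the change.

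**The concern.** A GEE models the marginal mean and handles within-person dependence through a working correlation. It has no random effects, so the random-intercept sentence cannot be carried out once GEE is primary. Two analysts following {20a} could fit different primary models.

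The choice interacts with missing data. A correctly specified likelihood mixed model is valid when dropout depends on scores already observed (MAR). For unweighted GEE on available data, the general guarantee covers only dropout that is completely at random, plus dropout explained by variables in the mean model. Beyond that, performance depends on the working correlation, which the plan does not state. If the random intercept is kept instead, it imposes one correlation for every pair of four visits, and the last visit is at three months and remote rather than face to face.

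At stake is the single estimate that answers Objective 1, for both primary outcomes. The recruitment target is just over 100 participants randomised 2:1, so TAU has about 34 (102/3).

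**Working it through.** **1. The plan's own figure.** Sample size {14} gives N = 90 for f = 0.15, two groups, two times, alpha 0.05 and power above 0.80. With noncentrality lambda = f²·N·m/(1-rho), m = 2 and an assumed rho = 0.5, lambda = 0.0225 × 90 × 2/0.5 = 8.1. On 1 and 88 df the power is 0.804, so the figure reproduces. It covers a two-time contrast and is silent on the four-visit model and on dropout.

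**2. Why the working correlation matters.** With a separate mean for each arm and visit and an identity link, independence GEE returns the raw mean of those still observed. Its bias in the contrast is the between-arm difference in [mean of those observed - mean of all]. If dropout depends only on arm or time, that bracket is zero within each arm. If dropout depends on earlier scores, it is not zero, and it cancels only if both arms lose similar people. A working correlation close to the truth uses the earlier scores to correct most of this.

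**3. First simulation.** All inputs are assumptions, because the documents give no dropout rates or correlations: n = 600,000, 2:1 allocation, SD 1, true contrast -0.50 SD, rho 0.5 or 0.7, true correlation compound symmetry (CS) or AR(1). Score-related dropout per visit follows logit(p) = -2.2 ± 1.0 × last score. Bias at follow-up:

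| Dropout (loss by follow-up) | Independence GEE | Exchangeable GEE |
|---|---|---|
| Completely at random (27%) | at most 0.005 | at most 0.005 |
| Arm only (METRA 19-20%, TAU 38-39%) | at most 0.004 | at most 0.004 |
| High scorers leave, same rule in both arms (27-32%) | +0.019 to +0.028 | +0.001 to +0.007 |
| High scorers leave METRA, low scorers leave TAU (27-36%) | -0.177 to -0.416 | about -0.015 (CS); +0.040 to +0.047 (AR(1)) |

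**4. Second simulation, with milder dropout.** Assumed: true effect -0.60 SD, 10% loss per visit after post-Module 1 (1 - 0.9² = 19% at follow-up), correlations decaying over time. Independence GEE at post-Module 2 / follow-up:

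| Scenario | Estimate | Relative error |
|---|---|---|
| High scorers leave METRA only | -0.65 / -0.67 | 0.05/0.60 = 8% / 0.07/0.60 = 12% |
| Low scorers also leave TAU | -0.68 / -0.71 | 0.08/0.60 = 13% / 0.11/0.60 = 18% |
| High scorers leave both arms, TAU loss doubled | -0.55 / -0.54 | 0.05/0.60 = 8% / 0.06/0.60 = 10%, toward zero |

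A repeat with baseline correlations 0.70/0.55/0.35 and 0.65, 0.45 and 0.55 among the later visits gave -0.66/-0.69, -0.72/-0.78 and -0.55/-0.52. The largest error is then 0.18/0.60 = 30%. Across both runs exchangeable GEE gave -0.57 to -0.62 (within 0.03/0.60 = 5%), and an unstructured covariance gave -0.60.

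**5. Scale against sampling error.** At N = 90, 2:1 and rho = 0.5, the variance of change is 2(1 - 0.5) = 1 and the SE is √(1/60 + 1/30) = 0.22 SD. The exchangeable error of 0.03 is about one-seventh of an SE. The 0.05 to 0.11 under independence is 0.2 to 0.5 of an SE.

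**6. If the random intercept is kept with model-based errors.** With the six correlations in step 4, the average is (0.70 + 0.55 + 0.35 + 0.65 + 0.45 + 0.55)/6 = 0.542. The model variance of change from baseline is 2(1 - 0.542) = 0.917 at every visit. The true variance is 2(1 - r), and type I error is 2[1 - Φ(1.96·√(0.917/true))].

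| Visit | r with baseline | True variance | Type I error |
|---|---|---|---|
| Post-Module 1 | 0.70 | 0.60 | 1.5% |
| Post-Module 2 | 0.55 | 0.90 | 4.8% |
| Follow-up | 0.35 | 1.30 | 10% |

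Equal correlation is too cautious at the first visit, about right at the second and too liberal at the last.

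**The case against.** The strongest reply is that this is an editing lapse with little numerical effect. The random-intercept sentence reads as carry-over from before the change note. For a continuous score with identity link, both models target the same arm-by-time contrast. The marginal counterpart of a random intercept is exchangeable correlation, so that is the natural reading of the GEE, and its error is small. The protocol also reports similar results from both models. No passage says dropout relates to symptoms: the stated reasons are security and movement, and loss that differs only by arm does no harm.

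Much of this stands. It lowers the likely size of the problem but does not supply the missing specification. The working correlation is still unstated, and step 3 shows that it decides whether bias is small or material. The similar results are weak reassurance, because exchangeable GEE and a random-intercept model nearly coincide for a linear outcome and so would agree whether or not dropout was informative. Neither addresses dropout that depends on unobserved scores.

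A reader might also infer that the N/A entry contradicts the intention-to-treat statement. It does not: baseline data are collected before randomisation ({16a}), so every randomised participant contributes data to either model.

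**Conclusion.** The point holds as a should-fix. The current text does not define one primary estimator, and it has no missing-data method where loss is expected, so validity under MAR dropout is not assured.

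Its size depends on choices the plan leaves open. Under assumed symptom-related dropout that differs by arm, independence GEE is off by roughly 8-18%, and by more when dropout is heavier or more strongly tied to scores. Exchangeable GEE is within about 5% in the milder setting and at most 0.05 SD in the harsher one. An unstructured likelihood model is unbiased. A retained random intercept can misstate standard errors in either direction by visit. The 10% figure belongs to follow-up only and applies only with model-based errors under the assumed correlations.

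Three stronger readings are not supported. Complete randomness of dropout is the general guarantee for unweighted GEE but not a necessary condition, as the arm-only rows show. Nothing shows that the trial's estimate is in fact biased, since the documents give no dropout rates or mechanism. And although results from both models were available when the note was written, the stated reason for the switch is reviewer feedback; nothing suggests GEE was chosen for its result.

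**What to change.** - In {20a}, name one primary model. The preferred choice is a REML repeated-measures model with arm, visit and arm-by-visit, unstructured covariance over the four visits, small-sample degrees of freedom (Kenward-Roger, for example) and all available data. A GEE with a stated working correlation and missing-data method would also close the gap in definition, but with weaker protection under MAR.
- Delete or reconcile the mixed-model, GEE and random-intercept sentences so that only one specification remains.
- Report GEE as a sensitivity analysis, with stated working correlation and robust variance, either inverse-probability weighted or on multiply imputed data.
- Replace N/A in {20c} with the MAR assumption and a delta-adjusted MNAR sensitivity analysis, and report dropout by arm and visit.
- State that the switch to GEE followed reviewer feedback, with results available.

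The cost is a few sentences of plan text and one re-run of the analysis. No new data are needed.

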**Interim analyses {21b}**

Not applicable

**Methods for additional analyses (e.g. subgroup analyses) {20b}**

Exploratory Analyses: Potential moderators (age, gender, trauma exposure, location, refugee experience) of intervention response will be explored with linear mixed models.

**Methods in analysis to handle protocol non-adherence and any statistical methods to handle**

**missing data {20c}**

N/A

**Plans to give access to the full protocol, participant level-data and statistical code {31c}**

N/A

## **Oversight and monitoring**

### **Composition of the coordinating centre and trial steering committee {5d}**

The Trial Steering Committee will provide overall supervision of the project. It will include independent members who will monitor trial progress, functioning of the partnership and ensure local and community involvement.

### **Composition of the data monitoring committee, its role and reporting structure {21a}**

Not applicable

### **Adverse event reporting and harms {22}**

Should an adverse effect be reported, the Chief Investigators will be notified immediately and a plan to resolve the serious adverse effect will be formulated. Depending on the nature of the adverse event, the Chief Investigators and research team will determine the appropriate course of action and then the research team will discuss the situation fully with the participant. A complete list of adverse effects, the steps taken to resolve them, and the results of those steps, will be reported to the Ethics Review Committee, Trial Steering Committee, Kabul University and Behrawan monthly, while serious adverse effects will be reported within one business day.

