#### **Interventions**

#### **Explanation for the choice of comparators {6b}**

Treatment as usual (TAU): Local NGOs will provide the course of intervention that they deem appropriate. No specific instructions will be given as to what TAU should entail, except not including elements specific to METRA. TAU will be documented ensuring understanding of the duration, frequency and type of treatment administered.

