### **Intervention description {11a}**

METRA: Module 1: Memory specificity training ([name] et al., 2018; Moradi et al., 2014; Neshat-Doost et al., 2013; Raes et al., 2009; Martens et al., 2019) is a manualized training delivered over five 60-minute sessions to groups of 6-8 adolescents. MEST aims to enhance memory specificity through practice. Session 1 provides psycho-education about mental health and memory.

Participants practice recalling memories in response to positive and neutral cues, with support from the group facilitator. Attention is paid to the contextual, spatio-temporal and sensory-perceptual details of the memories (Raes et al., 2009). Participants' responses are discussed in the group. At the end of the session, homework exercises are introduced; for 10 cues (positive and neutral) participants need to generate a specific memory and are instructed to write down a 'specific memory of the day' every evening of the coming week (Raes et al., 2009). Session 2 starts with a brief summary of Session 1, the homework exercises are discussed and the Session then follows the same format as Session 1, with further practice focusing on recalling memories in response to positive and neutral cues. At the end of Session 2, the homework is explained; participants need to generate two different specific memories for 10 cues (positive and neutral) and write down two different 'specific memories of the day' every evening of the coming week (Raes et al., 2009). Session 3 is very similar to Session 2. However, in Session 3, participants also need to work with negative cues. The homework exercises are similar to those outlined in Session 2, but now also include negative cues. Session 4 involves further exercises using negative and ('counterpart') positive cues. It is also explained how overgeneral thinking can be addressed by recalling a single specific experience and examples are discussed to promote metacognitive awareness of when participants are starting to shift to unspecific thinking or more general retrieval (Raes et al., 2009). Session 5 includes further practice and a summary of Module 1. Module 1 focuses on everyday remembering.

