Module 2: Writing for Recovery is a written exposure training involves five sessions (Kalantari et al., 2012; Sloan et al., 2018). In the first session the purpose of Module 2 is outlined. In the following sessions, the facilitator simply reads the instructions and the participant completes the writing task; writing about their trauma including thoughts and feelings. After 30 minutes, the facilitator instructs the participants to stop writing ([CHANGE 4: Timing of sessions reduced due to](#)

security concerns).

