### **Criteria for discontinuing or modifying allocated interventions {11b}**

Discontinue trial if participants report significant distress or a significant proportion of participants report significant increase in symptomatology. This will be based on the reports and observations of the facilitators and decisions to continue/discontinue will be made by the trial monitoring body.

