### **Data collection and management**

#### **Plans for assessment and collection of outcomes {18a}**

Data will be collected at; 1) baseline, 2) post-Module 1, 3) post-Module 2, and 4) ~~6-month~~ 3-month follow-up. Assessments will be conducted by independent raters who have no therapeutic relationship with participants and are blind to condition. All assessors will be trained and supervised in assessment procedures. All questionnaires have good reliability and validity and have been previously used cross-culturally.

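### Adverse effects enter the record only when someone reports them, and an observation route is described for METRA but not for TAU, so reported rates are open to unequal ascertainment by arm

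*Supplement*

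**What the plan says.** The adverse event section {22} is triggered by a report: "Should an adverse effect be reported, the Chief Investigators will be notified immediately". It then covers resolution, a monthly list to the oversight bodies, and faster handling of serious events ("while serious adverse effects will be reported within one business day"). It gives no definition of an adverse effect, no schedule or wording for asking about one, and no tabulation by arm.

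Contact differs between the arms. In {11a}, METRA Module 1 "is a manualized training delivered over five 60-minute sessions to groups of 6-8 adolescents", and the second module also has five: "Module 2: Writing for Recovery is a written exposure training involves five sessions". A facilitator is present in both modules. Section {11b}, on discontinuation, names its source of information: "This will be based on the reports and observations of the facilitators". Facilitators are described only for METRA.

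For the comparator, {6b} says "Local NGOs will provide the course of intervention that they deem appropriate". It adds that "TAU will be documented ensuring understanding of the duration, frequency and type of treatment administered"; adverse effects are not on that list. Section {16a} acknowledges that little that would count as TAU remains available.

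Both arms share one assessment schedule in {18a}: "Data will be collected at; 1) baseline, 2) post-Module 1, 3) post-Module 2", then a 3-month follow-up, with raters blind to condition.

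**The concern.** Under passive capture, the number of events recorded depends on how often a participant meets someone who will pass a report on. METRA participants meet trial facilitators repeatedly, and those facilitators are expected to observe. For TAU participants, no one outside the scheduled assessments is described as passing adverse effects to the trial. Two arms with the same true event rate could then show different recorded rates.

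This matters because Module 2 asks distressed adolescents to write about their trauma, so readers will want to know whether it was tolerated. A recorded excess in METRA could reflect only closer observation. An event in TAU that the scales do not register could be missed. Either error would also weaken what can be said about appropriateness, a secondary objective.

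**Working it through.** The plan gives no figure for adverse-effect reporting, so there is none to reproduce. The check has two parts.

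**Text side by side**

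| Question | METRA | TAU |
|---|---|---|
| Sessions described | 5 + 5 = 10, facilitated ({11a}) | Left to the NGOs ({6b}) |
| Observer who feeds information on harm | Facilitators ({11b}) | None described |
| What is documented about care | Sessions audio-recorded, 25% rated for adherence ({11c}) | Duration, frequency and type ({6b}) |
| Scheduled question on adverse effects | None ({22}) | None ({22}) |
| Blinded assessments after randomisation | 3 ({18a}) | 3 ({18a}) |

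**Illustration of size**

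Let *q* be the chance that an existing event comes to light at any one contact, and *k* the number of contacts after randomisation that can lead to a report. Treating contacts as independent, and the event as reportable at each of them, the share of events captured is 1 − (1 − *q*)^*k*.

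- METRA: *k* = 10 sessions + 3 assessments = 13.
- TAU: *k* = 3, assuming that NGO contacts yield no reports to the trial.
- *q*: assumed, because the documents give no reporting rate.

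Example for *q* = 0.10: METRA 1 − 0.90^13 = 0.746; TAU 1 − 0.90^3 = 0.271; ratio 2.75.

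| *q* (assumed) | METRA captured | TAU captured | Spurious ratio |
|---|---|---|---|
| 0.05 | 0.487 | 0.143 | 3.41 |
| 0.10 | 0.746 | 0.271 | 2.75 |
| 0.20 | 0.945 | 0.488 | 1.94 |
| 0.30 | 0.990 | 0.657 | 1.51 |
| 0.50 | 1.000 | 0.875 | 1.14 |

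The true event rate is the same in both arms and cancels from the ratio.

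The assumption about NGO contacts matters most. With five NGO contacts that can lead to a report (TAU *k* = 8), the ratio is 1.31 at *q* = 0.10 and 1.05 at *q* = 0.30. With ten (TAU *k* = 13), it is 1.0 for any *q*.

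These are ratios of proportions. Under the 2:1 allocation in {16a}, raw event counts would differ by a further factor of 2, so counts need their denominators.

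**The case against.** The strongest reply is that the harm of most interest, worsening symptoms in adolescents doing trauma writing, is already measured without this bias. PTSD, depression, anxiety, Afghan-specific symptoms and internalising/externalising problems ({12}) are assessed in both arms on one schedule by blinded raters. This stands. A reader might infer that harms cannot be compared between the arms at all; the documents do not support that. The exposed part is narrower: events that reach the record only through spontaneous report. The scales do not close that gap, because they are planned only as efficacy outcomes and include no direct question about adverse events.

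A reader might also infer that TAU participants have no contact with the trial between assessments. No section says so, and the promise to document TAU implies some flow of information from the NGOs. What can be said is that no adverse-effect route is described.

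Thirdly, {22} names no reporter and no arm, so an effect mentioned to anyone in either arm falls under it. Facilitator observation comes from {11b}, a separate rule. That is correct: the wording of {22} is even-handed. The inequality comes from applying an even-handed passive rule to arms with different described opportunities to report.

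Finally, no between-arm analysis of adverse events is promised, so no planned comparison is broken. This also stands and limits the weight of the point. It does not remove it, because recorded events from a randomised trial are likely to be read by arm whether or not a test is planned.

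**Conclusion.** The point holds in limited form. As written, the plan leaves rates of spontaneously reported adverse effects open to unequal ascertainment, in a direction that would tend to make METRA look worse than TAU. Symptom worsening on the scales remains comparable.

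The size is unknown. The range of about 3.4 down to 1.1 rests on assumed per-contact reporting chances of 0.05 to 0.50 and on NGO contacts producing no reports. If TAU contacts feed reports to the trial as METRA sessions do, the ratio is 1.0. The figures show that the bias could be material; they do not predict that it will occur. This is a worthwhile low-cost improvement to {22}, and it does not bear on the primary efficacy analysis.

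**What to change.** In {22}, add one identical adverse-effect question for the blinded assessors to put to every participant in both arms at post-Module 1, post-Module 2 and the 3-month follow-up. Ask it after the outcome scales are complete, in neutral wording that does not mention sessions, groups or writing.

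Base any between-arm statement on harms on these solicited answers, shown as proportions of those asked in each arm. Tabulate events learned only through facilitators separately, and do not use them for the comparison. Leave the notification and reporting steps as they are.

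No extra visits or staff are needed. There are two costs. Assessments become slightly longer, and the abstract of Version 2 explains that they had to be kept short for safety; a positive answer will also need some follow-up. There is also a small risk that an answer reveals allocation. Asking last protects that visit's scales, but the same rater could be unblinded for later visits.
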